# Dichloroacetate as a possible treatment for endometriosis-associated pain: a single-arm open-label exploratory clinical trial (EPiC)

**DOI:** 10.1186/s40814-021-00797-0

**Published:** 2021-03-12

**Keywords:** Chronic pelvic pain, Gynaecology, Glycolysis, Repurposing, Feasibility trial

## Abstract

**Background:**

Endometriosis (where endometrial-like tissue is found outside the uterus) affects ~ 176 million women worldwide and can lead to debilitating pelvic pain. There is an unmet need for new medical treatment options for endometriosis. Pelvic peritoneal mesothelial cells of women with endometriosis exhibit detrimental metabolic reprogramming that creates an environment favouring the formation and survival of endometriosis lesions. We have generated powerful preclinical proof-of-concept data to show that it is possible to correct this metabolic phenotype using dichloroacetate (DCA), a non-hormonal compound previously used to treat rare metabolic disorders in children. We plan a single-arm, open-label, single site exploratory clinical trial to inform the design of a future randomised controlled trial (RCT) to determine the efficacy of DCA for the treatment of endometriosis-associated pain.

**Methods:**

We will recruit 30 women with endometriosis-associated pain over a 6-month period. All participants will receive approximately 6.25 mg/kg oral DCA capsules twice daily for 6 weeks, with a dose increase to approximately 12.5 mg/kg twice daily for a further 6 weeks if their pain has not been adequately controlled on this dose regime and side-effects are acceptable. If pain is adequately controlled with minimal side-effects, the lower dose will be continued for a further 6 weeks. The primary objective is to determine whether it is possible to achieve acceptable recruitment and retention rates within the defined exclusion and inclusion criteria. Secondary objectives are to determine the acceptability of the trial to participants, including the proposed methods of recruitment, treatment, follow-up frequency and number of questionnaires. The recruitment rate will be determined by the proportion of patients recruited from the pool of eligible women. The retention rate will be determined by the proportion of participants who attended the final trial visit.

**Discussion:**

This is a feasibility study to explore effectiveness and acceptability of the proposed field methodology (recruitment, retention, study processes and compliance with treatment). The results will be used to inform the design of a future RCT.

**Trial registration:**

ClinicalTrials.gov, NCT04046081 Registered 6 August 2019

## Background

Endometriosis is characterised by the presence of endometrial-like tissue outside the uterus, commonly on the lining of the pelvic cavity [1]. It is a chronic, inflammatory gynaecological condition that affects approximately 10% of women of reproductive age [2]. It is associated with debilitating pelvic pain, pain during menstruation, pain during intercourse and subfertility [3, 4]. Direct healthcare costs amount to nearly 3000 Euros per woman per year (based on 2009 prices), similar to those of diabetes mellitus [5]. Current treatment options are often unsatisfactory. Of women undergoing surgery, over half would have a further surgical procedure by 5 years [6]. Available hormonal treatments have unwanted side-effects and are contraceptive [7]. There is an ‘unmet need for new medical treatments for endometriosis’ which are disease modifying and fertility sparing [8].

Endometriosis exhibits cancer-like features [9]. Specifically, tumour cells are programmed by TGF-β1 to use aerobic glycolysis resulting in increased secretion of lactate [10–12]. We have shown that TGF-β1 and lactate are both elevated in the peritoneal fluid of women with endometriosis and that this is paralleled by a switch from normal mitochondrial respiration towards glycolysis in the human peritoneal mesothelial cells (HPMC) that line the pelvic cavity [10–12]. In the tumour microenvironment, lactate is considered a key factor in driving cell invasion, angiogenesis and immune suppression [13], all of which are implicated in the establishment and survival of endometriosis lesions. Using in vitro models, we have demonstrated that the glycolysis inhibitor, dichloroacetate (DCA), reversed the aberrantly increased glycolysis of HPMC and oral administration of DCA reduced the size of endometriosis lesions in a mouse model [14].

We plan a single-arm open-label exploratory clinical trial to determine the feasibility of achieving an acceptable recruitment and retention rates. This trial will inform the design of a potential future large randomised controlled trial (RCT) to determine the efficacy of DCA to treat women with endometriosis-associated pain.

## Methods/design

### Primary outcome

To determine whether it is possible to achieve acceptable recruitment and retention rates within the defined inclusion/exclusion criteria

### Secondary outcomes

To determine the acceptability to participants of the proposed method of recruitment, treatment, questionnaires and follow-up (e.g. frequency and method for collecting pain scores and for completion of questionnaires)To assess how well-tolerated is DCA in women with endometriosisTo determine if we can detect systemic DCA in blood samples of women with endometriosisTo determine participants’ compliance with treatment and to assess the tools used to measure compliance

### Study design

This is a single site, open-label exploratory study of women with endometriosis.

### Study population

We will recruit 30 women with endometriosis-associated pain over a 6-month period. The duration of the entire trial will be 12 months. The trial visits will take place within NHS Lothian, UK. The participants will be required to come to the hospital for five visits, at day 1 and at weeks 2, 6, 8 and 12 to complete questionnaires, give blood samples and receive further DCA supplies if required. The participants will be taking the treatment for 12 weeks and will receive a phone call 4 weeks (± 1 week) after the last date of treatment to ask about their general health and how satisfied they are with the treatment and trial methods (see Table 1).

**Table 1 Tab1:**
[figure not shown]
Summary of study visits and assessments

### Inclusion criteria

Pre-menopausal women aged 18 or overWeight between 50 and 100 kgSuperficial peritoneal endometriosis (ASRM stage I or II) identified at laparoscopy, performed within the last five years (and > 2 weeks from surgery)Pelvic pain for longer than 6 monthsAverage pain score of ≥ 4 over the 4 weeks prior to treatmentWilling to comply with the treatmentWilling to use non-hormonal contraception throughout the trialWilling and able to complete informed consent

### Exclusion criteria

Evidence of ovarian endometrioma or deep endometriosis (based upon current surgical staging or most recent imaging)Women who are pregnant or actively trying to get pregnantKnown allergy or hypersensitivity to any excipient of DCABreastfeedingClinical evidence of pre-existing peripheral neuropathyDiabetes, history of liver, or history of kidney diseaseTaking part in another Clinical Trial of an Investigational Medicinal Product (CTIMP) or other interventional non-CTIMP studiesPatient on combination anti-retroviral therapyHistory of malabsorption syndrome or substantial amount of small bowel or stomach removed

### Participant enrolment

Potentially eligible women will be asked by their attending clinician if they would be interested in participating in the study. If they agree, the women will then be given a patient information sheet and will be referred to members of the clinical research team to discuss the study in more detail. Patients will be allowed to self-refer to the study by contacting the research team directly. Informed consent will only be taken by a member of the research team once the participants have had ample time (at least 24 h) to read the patient information sheet and had their questions answered. Following consent, eligibility will be assessed by the clinical team. A screening log will be maintained and the following anonymised information will be monitored and collected for all potential participants: date of attendance in clinic, year of birth, reason for non-eligibility and reason for not participating if eligible and willing to give a reason. Ineligible and non-recruited participants will be offered routine NHS gynaecological care.

### Intervention

Based on our current preclinical studies and the current literature, we have chosen a dose which will potentially be effective for endometriosis-associated pain and has the least side-effects. Trials using DCA as a potential treatment for cancer or pulmonary arterial hypertension suggest that doses of 6.25 mg/kg BD should produce blood levels within the range required for pyruvate dehydrogenase kinase (PDK) inhibition, although DCA pharmacokinetics may be variable [15]. We also note that most side-effects, such as reversible peripheral neuropathy, seem to occur at doses of 25–50 mg/kg/day [16–18]. We therefore plan to trial the feasibility of a dose change with DCA at approximately 6.25 mg/kg BD (oral) for 6 weeks, followed by a dose increase to approximately 12.5 mg/kg BD (oral) for the next 6 weeks, depending on participant’s tolerance of treatment (total treatment phase of 12 weeks).

The drug will be provided in capsules containing 333 mg or 500 mg of DCA powder (Curaltus Ltd, Lithuania). Participants will be required to take between two to six capsules orally a day depending on the dose calculated using their body weight. The drug will be dispensed on day 1 of treatment and resupplied if needed at each visit during week 2, 6 and 8. Sufficient amount of drug will be provided to last until the next visit or end of study.
*Weeks 1–6*. All participants will receive approximately 6.25 mg/kg BD daily (oral) for 6 weeks.*Weeks 6–12*. Dosing may be escalated depending on symptom control and side-effects (options 1–3 as below).
*Option 1*. If the participant still has painful symptoms at the end of week 6 and minimal or no side-effects, she will be asked to increase the dose of DCA to approximately 12.5 mg/kg BD daily (oral) for a further 6 weeks (see Figure 1, study flow chart). Dose escalation will be overseen by a medical doctor on the delegation log.*Option 2*. If DCA has been helpful in reducing painful symptoms and caused minimal side-effects, then the participant will be asked to continue to take DCA 6.25 mg/kg BD daily (oral) for a further 6 weeks.*Option 3*. If the participant suffers from side-effects from DCA and the dose of DCA taken does not provide relief for endometriosis pain, the participant is allowed to stop taking the drug at any stage of the treatment, but they will continue to be followed up with their consent.

**Fig. 1 Fig1:**
[figure not shown]
Study Flow chart. DCA, Dichloroacetate. NRS, Numerical Rating Scale

If participants who take 12.5 mg/kg BD (oral) have side-effects and do not tolerate the treatment, they will be allowed to return to low dose of 6.25 mg/kg BD. If participants do not have enough capsules to return to low dose, they will be resupplied with new capsules.

### Assessment of participant compliance

Participants will be asked about compliance at each visit, which will be recorded in the case report form (CRF). Compliance will be also measured via a treatment diary and systemic blood levels.

### Other medications

Participants will be allowed to take any oral analgesics and alternative treatments (e.g. acupuncture) throughout the study period, which will be recorded in the CRF. Due to the potential for pain relief from hormonal therapy, patients will only be allowed to take hormonal therapies if they have started them more than three months before consent.

### Safety assessments

At the first visit, a medical history will be taken to assess specific eligibility points, such as concurrent neuropathy, diabetes, liver or kidney disease, anti-retroviral use and use of concomitant medications. Contraception requirement and method will be documented and a pregnancy test undertaken. Participants will be assessed at each visit by a Good Clinical Practice (GCP)-trained medical doctor to confirm their wellbeing, including a neurological examination to assess for peripheral neuropathy.

### Study assessments

Study visits and assessments are outlined in Table 1. Stage of cycle will be documented at commencement of treatment.

Quality of Life and pain questionnaires include the Endometriosis Health Profile-30 [19], PainDETECT^TM^ [20], Brief Fatigue Inventory (BFI) [21] and Pain Catastrophising Questionnaire [22]. At the end of the study (week 16) participants will be asked to complete an acceptability questionnaire, using a five point Likert scale. This consists of 11 questions to record acceptability of the proposed methods of recruitment, follow-up, treatments and use of quality of life and pain questionnaires. All questionnaires will be completed in private and anonymised. Patients will have a choice to complete them on paper during their visit or at home using an online link to secure REDCap database. Numerical Rating Scale (NRS) for pain will be collected on paper CRF only and will be recorded on the database that they were completed.

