### Termination of study

All participants will be required to stop DCA treatment after 12 weeks and return any remaining DCA to the investigator at the end of the study. Participants may withdraw from the trial at any point or a participant can be withdrawn by the investigator. Although pregnancy is not considered an adverse event, any participant’s pregnancy will be recorded on a Pregnancy Notification Form and submitted to the ACCORD office within 14 days of being made aware of the pregnancy. All pregnant participants will be followed up until the outcome of the pregnancy. Data collection is envisaged to be completed in August 2020.

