### Primary endpoint

The primary endpoint is to determine recruitment and retention rates. Using the information collected from the participant log, we will determine the number of patients recruited from the pool of eligible women and a 50% of 60, 95% CI (36.8–63.2%) recruitment will be deemed acceptable. While a retention rate of 100% would be ideal, we will consider a rate of 80% satisfactory. We will provide an estimate of the proportion and its 95% CI (61.4–92.3%). In addition, we will determine the nature and number of unanswered questions in each questionnaire. We aim to determine whether the trial design will perform well enough in the field to warrant rolling out the study to full trial. All analysis will be carried out in the University of Edinburgh.

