### Secondary endpoints

Acceptability of proposed methods of recruitment, follow-up, treatments and questionnaires used in this study will be assessed quantitatively using self-reported side-effects and acceptability questionnaires at the end of study. We also aim to determine if treatment is acceptable in terms of self-reported compliance (from treatment diaries). The blood samples collected from patients will be analysed at University of Edinburgh, QMRI, to detect the systemic levels of DCA to confirm participants’ compliance. The assay will be developed in the research laboratory of the Edinburgh Clinical Research Facility. It will be analysed using mass spectrometry (choosing the instrument that will provide most accurate readings) and either Analyst MultiQuant software or Xcalibur Quantitate software. Descriptive statistics will be used to describe use of rescue analgesia, side-effects and compliance and will be compared by dose escalation or not.

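### The acceptability questionnaire has one stated time, week 16, and none is described at withdrawal, so acceptability among responders may be overstated

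*Protocol article*

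**What the plan says.** Acceptability to participants is listed first under Secondary outcomes in the Protocol article. Its dedicated instrument is described under Study assessments: "At the end of the study (week 16) participants will be asked to complete an acceptability questionnaire", on a five-point Likert scale. On content: "This consists of 11 questions to record acceptability of the proposed methods of recruitment, follow-up, treatments and use of quality of life and pain questionnaires". Under Secondary endpoints, acceptability "will be assessed quantitatively using self-reported side-effects and acceptability questionnaires at the end of study". The timing is thus stated twice, and both statements place it at the end.

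Termination of study says: "Participants may withdraw from the trial at any point or a participant can be withdrawn by the investigator". It mentions no acceptability form at that moment.

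Four other provisions bear on the point:
- Intervention, Option 3: a woman who stops DCA remains in follow-up if she consents.
- Study population: a telephone call, 4 weeks (± 1 week) after the last treatment date, asks about general health and about satisfaction with treatment and trial methods.
- Adverse events: known side-effects are entered on the case report form at each visit.
- Participant enrolment: a screening log holds reasons for not taking part, where women give them.

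The planned number is 30 women. For retention, Primary endpoint says "we will consider a rate of 80% satisfactory". The Abstract defines retention as attendance at the final trial visit.

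**The concern.** The questionnaire asks about treatment, follow-up and questionnaire load. These are plausible reasons for a woman to leave the trial. A form whose only stated time comes after the losses have happened tends to be answered by those for whom the trial was tolerable. Non-response is then likely to be informative, with overstatement the plausible direction.

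The trial exists to inform the design of a randomised trial, and the Discussion says that procedures will be revised if acceptability problems appear. Women who left are the most direct source on what needs revising. The retention rate will show that they left. It will not show which feature of the trial was the cause.

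**Working it through.** **1. The plan's own figure.** With 30 women and 80% retention, 0.80 × 30 = 24 are retained and 30 − 24 = 6 are lost. The exact (Clopper-Pearson) 95% interval for 24/30 has as limits the 2.5% quantile of Beta(24, 7) and the 97.5% quantile of Beta(25, 6), which gives 61.4% to 92.3%. This matches the interval under Primary endpoint, so 24 of 30 is the scenario that the article has in mind. The article gives no figure for acceptability, so every acceptance rate below is an assumption.

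**2. Formula.** Let N = 30 be enrolled and m give no answer. Let p be the share accepting among the N − m who answer, and q the unknown share accepting among the m who do not. Then

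- share over all enrolled = [p(N − m) + qm]/N
- overstatement by the responder figure = p − that share = (m/N)(p − q)

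The largest overstatement is at q = 0 and equals p × m/N. At q = 1 the responder figure is too low, by (1 − p) × m/N.

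**3. Numbers put in.**

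| Answering | Accepting | Reported | Worst case over 30 (q = 0) | Best case over 30 (q = 1) | Largest overstatement |
|---|---|---|---|---|---|
| 24 | 24 | 100% | 24/30 = 80.0% | 30/30 = 100% | 20.0 points |
| 24 | 22 | 91.7% | 22/30 = 73.3% | 28/30 = 93.3% | 18.3 points |
| 24 | 19 | 79.2% | 19/30 = 63.3% | 25/30 = 83.3% | 15.8 points |
| 27 | 27 | 100% | 27/30 = 90.0% | 30/30 = 100% | 10.0 points |
| 27 | 22 | 81.5% | 22/30 = 73.3% | 25/30 = 83.3% | 8.1 points |
| 30 | any | p | p | p | 0 |

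**4. A less extreme case.** If women who do not answer are half as accepting as responders (q = p/2), the overstatement halves. At 22/24 it is 0.2 × 0.917/2 = 9.2 points, for a true share of 82.5%. At 19/24 it is 7.9 points, for a true share of 71.3%.

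**5. How many answers might be missing.** Six is borrowed from the retention target, and retention is not the same as response. Retention is judged at the final trial visit. The last hospital visit listed under Study population is week 12, and only the telephone call follows it. A woman can therefore count as retained and still not answer at week 16. Conversely, the form can be completed at home by an online link, so a woman who missed the final visit can still answer. With 9 missing and every responder accepting, the largest overstatement would be 9/30 = 30 points.

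**The case against.** The strongest case against is that the article has more in place than the timing sentence suggests, and several stronger readings that a reader might reach are not supported.

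- *That only completers are asked.* The article says participants and sets no such limit, and the online link removes the need to attend.
- *That the views of women who leave are never sought.* The satisfaction call is timed from the last treatment date, so for a woman who stops early it can fall before week 16. The article does not say whether women who have withdrawn from the trial are called, and Secondary endpoints does not name the call as a source for acceptability. It narrows the gap without closing it.
- *That women who find the drug unacceptable are missing.* They may stop it and stay in follow-up. They are missing only if they also leave the trial or do not answer.
- *That problems with recruitment are hidden.* Women put off by recruitment do not enrol. Their reasons go to the screening log, and no change to the questionnaire's timing would reach them.
- *That the result is biased upwards.* It may be. The largest figures need every missing woman to find the trial unacceptable, and the Discussion expects some non-attendance because of Covid-19, which says little about acceptability.

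Two more points have weight. Side-effects recorded at each visit also feed the endpoint, so women who leave contribute up to that time, though on tolerability rather than on visit or questionnaire burden. And an exit procedure may exist in the full protocol, while Table 1 and Figure 1 could not be read for this check. Silence on exit procedures alone would be no finding. What stands is that the article positively fixes the instrument's time, twice, after the losses will have occurred.

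**Conclusion.** The point holds in a limited form. The only stated time for the dedicated questionnaire is week 16, and the article describes no collection from women who withdraw earlier. Acceptability among responders may therefore be overstated.

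With 24 of 30 answering, the ceiling is 20 points if all responders accept and about 18 points at an assumed 22/24. It is nil if nobody is missing or if those missing are as accepting as those who answer. These are bounds, not estimates. They rest on an assumed response of 80%, on assumed acceptance rates, and on reducing Likert answers to accepting or not, for which the article gives no cut-off. The outcome is secondary and descriptive, so the primary assessment of recruitment and retention is untouched.

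**What to change.** 1. Under Study assessments, state that the existing 11-item questionnaire is also offered when a woman withdraws from the trial, by the existing REDCap link or by telephone, as well as at week 16.
2. Under Secondary endpoints, state that acceptability is reported with the number of enrolled women who did not answer. Beside the responder figure, give worst-case and best-case bounds over all enrolled women, x/N and (x + m)/N, where x is the number accepting. The worst case is to be presented as a bound only, since some non-response will have other causes.

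The cost is about six extra form offers at 80% retention and one further line of analysis. Some women who withdraw will not answer, and with 30 women the bounds may be wide: 20 points at six missing. The second step needs no new data, so it remains possible if follow-up has already closed.
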